# 1 Background

According to the World Health Organization (WHO) report in 2005, there are 400,000 new colorectal cancer patients annually in China. Colorectal cancer has become the third-leading cause of cancer-related death in Chinese patients, with an annual mortality rate of 16.83 per 100,000. Low and mid rectal cancers account for approximately 70% to 80% of rectal cancers in China. Total mesorectal excision (TME) is still the primary treatment for rectal cancer. Recent studies have shown that laparoscopy-assisted resection is safe for treating low rectal cancer. It has the advantages of minimally invasive procedures: faster postoperative recovery, less pain, shorter hospital stay, and long-term efficacy comparable to open surgery.

Randomized control trials with large samples were launched to investigate laparoscopic and open surgery for colorectal cancer in European and North American countries, including the CLASSIC trial, the COLOR trial, and the COST study. These studies compared the completeness of tumor resection, long-term efficacy, and patient's Quality of life (QoL) between the two surgical approaches. The results showed that laparoscopic resection did not increase complications or operative mortality compared with open resection in treating rectal cancer. The two surgeries were comparable in the distance and negative rate of pathological resection margins (proximal, distal, and circumferential) and the number of dissected lymph nodes. Many meta-analyses have found no significant differences between the two surgical approaches in local recurrence rate, distant metastasis rate, or disease-free survival (DFS) rate.

Recent studies have also shown that laparoscopic total mesorectal excision (TME) for rectal cancer after preoperative chemoradiotherapy is safe without increasing the incidence of surgery-related complications or mortality. Moreover, with the accumulation of surgical experience and skills, the conversion rate from laparoscopic surgery to open surgery gradually decreases. However, the interpretation of these findings needs to be further discussed.

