## **2 Objective**

To evaluate the perioperative safety and long-term efficacy of laparoscopy-assisted surgery for low rectal cancer compared to open surgery.

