### 8.3.3 Outcome analysis

- **Analysis of primary outcome measures**

The DFS is calculated using the Kaplan-Meier method after the last participant has been enrolled for three years. The median DFS time and its 95% confidence interval are compared between the two groups using the log-rank test. Cox regression is used to calculate the hazard ratio and its one-sided 95% confidence interval between the two groups. According to the prespecified noninferiority criteria, the inferiority of the treatment to be tested compared with the control treatment is determined.

- **Analysis of secondary outcome and other pre-specified outcome measures**

(1) Pathologic outcomes, including the TME quality, negative CRM, and negative DRM, are presented as numbers (percentage) and compared using the Chi-square test.

(2) The operation time (min) and estimated blood loss (ml) are compared between the groups by the Wilcoxon method.

(3) The OS is calculated using the Kaplan-Meier method after the last participant has been enrolled for three years. The median OS time and its 95% confidence interval are compared between the two groups using the log-rank test.

(4) The OS when the last participant is enrolled for five years is determined by using the Kaplan-Meier method. The median OS time and its 95% confidence interval are compared between the two groups using the log-rank test.

(5) Time to tumor recurrence is determined using the Kaplan-Meier method. The median time of recurrence and its 95% confidence interval are compared between the two groups using the log-rank test.

(6) The perioperative recovery time is compared between the groups using the Wilcoxon method.

(7) The length of postoperative hospital stay (d) is compared between the groups using the Wilcoxon method.

(8) The incidence of intraoperative complications is compared between the groups by the  $\chi^2$  test or Fisher's exact probability method.

(9) After surgery, the incidence of complications and 30-day mortality rate are compared using the  $\chi^2$  test or the Fisher's exact tests for probability.

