#### **8.4 Statistical software and general requirements**

(1) SAS 9.4 is used for analysis (SAS Institute Inc., Cary, NC, USA).

(2) Generally, two-sided tests are used for statistical analysis, and a  $P$  value  $< 0.05$  indicates that the difference is statistically significant.

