| Negative PRMs, No. (%)                |                                           |                                   |                              | X.XXX          |
| Overall group                                | XXX(XX.X)                                 | XXX(XX.X)                         |                              |                |
| Stage I disease                              | XXX(XX.X)                                 | XXX(XX.X)                         |                              |                |

|                                    |           |           |  |       |
|------------------------------------|-----------|-----------|--|-------|
| Stage II/III disease               | XXX(XX.X) | XXX(XX.X) |  |       |
| Negative DRMs, No. (%)      |           |           |  | X.XXX |
| Overall group                      | XXX(XX.X) | XXX(XX.X) |  |       |
| Stage I disease                    | XXX(XX.X) | XXX(XX.X) |  |       |
| Stage II/III disease               | XXX(XX.X) | XXX(XX.X) |  |       |
| Negative CRMs, No. (%)      |           |           |  | X.XXX |
| Overall group                      | XXX(XX.X) | XXX(XX.X) |  |       |
| Stage I disease                    | XXX(XX.X) | XXX(XX.X) |  |       |
| Stage II/III disease               | XXX(XX.X) | XXX(XX.X) |  |       |
| Pathologic T stage, n (%)   |           |           |  | X.XXX |
| T0/Tis                             | XXX(XX.X) | XXX(XX.X) |  |       |
| T1                                 | XXX(XX.X) | XXX(XX.X) |  |       |
| T2                                 | XXX(XX.X) | XXX(XX.X) |  |       |
| T3                                 | XXX(XX.X) | XXX(XX.X) |  |       |
| T4a                                | XXX(XX.X) | XXX(XX.X) |  |       |
| T4b                                | XXX(XX.X) | XXX(XX.X) |  |       |
| Pathologic N stage, n (%)   |           |           |  | X.XXX |
| N0                                 | XXX(XX.X) | XXX(XX.X) |  |       |
| N1a                                | XXX(XX.X) | XXX(XX.X) |  |       |
| N1b                                | XXX(XX.X) | XXX(XX.X) |  |       |
| N1c                                | XXX(XX.X) | XXX(XX.X) |  |       |
| N2a                                | XXX(XX.X) | XXX(XX.X) |  |       |
| N2b                                | XXX(XX.X) | XXX(XX.X) |  |       |
| Pathologic TNM stage, n (%) |           |           |  | X.XXX |

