**Table 6. Postoperative Recovery and Complications**

| Characteristics                                    | Laparoscopic Surgery Group (n=XXX) | Open Surgery Group (n=XXX) | Difference, % (95% CI) | P value |
|----------------------------------------------------|------------------------------------|----------------------------|------------------------|---------|
| Postoperative recovery                      |                                    |                            |                        |         |
| Time to first flatus, median (IQR), h              | XX (XX.X–XX.X)                     | XX (XX.X–XX.X)             |                        | X.XXX   |
| Time to first defecation, median (SD), h           | XX (XX.X–XX.X)                     | XX (XX.X–XX.X)             |                        | X.XXX   |
| Time to liquid diet, median (IQR), h               | XX (XX.X–XX.X)                     | XX (XX.X–XX.X)             |                        | X.XXX   |
| Time to resumption of normal diet, median (IQR), h | XX (XX.X–XX.X)                     | XX (XX.X–XX.X)             |                        | X.XXX   |
| Time to analgesic requirement, median (IQR), h     | XX (XX.X–XX.X)                     | XX (XX.X–XX.X)             |                        | X.XXX   |
| Postoperative hospital stays, median (IQR), d      | XX (XX.X–XX.X)                     | XX (XX.X–XX.X)             |                        | X.XXX   |
| Postoperative 30-day complications, n (%)   | XXX(XX.X)                          | XXX(XX.X)                  |                        | X.XXX   |
| Presacral hemorrhage                               | XXX(XX.X)                          | XXX(XX.X)                  | XX (XX.X–XX.X)         | X.XXX   |
| Active intraabdominal bleeding                     | XXX(XX.X)                          | XXX(XX.X)                  | XX (XX.X–XX.X)         | X.XXX   |
| Anastomotic bleeding                               | XXX(XX.X)                          | XXX(XX.X)                  | XX (XX.X–XX.X)         | X.XXX   |
| Anastomotic leakage                                | XXX(XX.X)                          | XXX(XX.X)                  | XX (XX.X–XX.X)         | X.XXX   |
| Chylous leakage                                    | XXX(XX.X)                          | XXX(XX.X)                  | XX (XX.X–XX.X)         | X.XXX   |

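### Total 30-day complications, 30-day mortality and margin status are judged only by tests of no difference, with no risk-difference interval planned, although perioperative safety is half of the objective

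*Combined protocol and SAP*

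**What the plan says.** SAP section 2 gives the objective as "To evaluate the perioperative safety and long-term efficacy of laparoscopy-assisted surgery for low rectal cancer compared to open surgery". Pathologic outcomes (including CRM and DRM status), 30-day complications and 30-day mortality are named secondary outcomes in SAP 7.2. The only noninferiority margin in either document is 10% on 3-year DFS (SAP 8.1).

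SAP 8.3.3 sets the comparisons:

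- Item (1): "Pathologic outcomes, including the TME quality, negative CRM, and negative DRM, are presented as numbers (percentage) and compared using the Chi-square test".
- Item (9): "After surgery, the incidence of complications and 30-day mortality rate are compared using the" chi-square or Fisher's exact test. Item (8) allows the same choice for intraoperative complications.

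SAP 8.4 adds "Generally, two-sided tests are used for statistical analysis", with significance at P<0.05. Protocol 12.2(3) and 12.3 match. No sentence says how a non-significant safety result is to be read, and SAP section 10, on statistical conclusions, has a title but no text.

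The shells in SAP section 9 have a column for the percentage difference with its 95% CI:

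| Row | Difference and 95% CI cell |
|---|---|
| TME quality, overall and by stage (Table 5) | interval |
| Negative DRM and CRM, overall and by stage (Table 5) | blank |
| Total 30-day complications (Table 6) | blank |
| Each listed complication (Table 6) | interval |
| 30-day mortality (Table 6) | count-and-percentage placeholder, not an interval |
| Each Clavien-Dindo grade (Table 6) | interval |

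**The concern.** For the rows that best summarise perioperative safety and margin clearance, the plan provides group percentages and a P value. A test of no difference that fails to reject does not show that two operations are equally safe. It may only mean that the trial was too small to see the harm. Here failure to reject is also the result that favours the experimental operation. The efficacy half of the objective has to exclude a stated loss, whereas the safety half only has to avoid significance in a trial sized for DFS. An interval for the risk difference would show how much excess risk the data leave open.

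A smaller problem lies in item (1). It names the chi-square test alone for margin status, while items (8) and (9) allow an exact test. With about 2:1 allocation and very few events, the chi-square test is not symmetric between the arms.

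**Working it through.** **Inputs.** Arm sizes are 646 laparoscopic and 322 open in total, 240/119 in stage I and 406/203 in stage II/III (SAP 8.1). The test is two-sided at 5% (SAP 8.4). The documents give no event rates and no relevant harm size for these outcomes, so every rate below is an assumption shown as a range. They also state no power for these outcomes, so there is no planned figure to reproduce.

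**Step 1: chance of missing a true laparoscopic harm.** Take both arms as binomial, apply the test to every possible pair of counts, and add up the probability of P>=0.05. The test is the uncorrected Pearson chi-square for complications and CRM, and Fisher's test for mortality.

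| Outcome | Open vs laparoscopic | Missed |
|---|---|---|
| Total complications | 10% vs 15% | 41% |
| | 15% vs 20% | 52% |
| | 20% vs 25% | 59% |
| | 15% vs 25% | 4% |
| | 20% vs 30% | 8% |
| Positive CRM | 2% vs 5% | 34% |
| | 3% vs 6% | 46% |
| | 5% vs 8% | 60% |
| | 3% vs 8% | 10% |
| Positive CRM, stage I | 3% vs 6% | 79% |
| Positive CRM, stage II/III | 3% vs 6% | 64% |
| 30-day mortality | 0.5% vs 1.5% | 81% |
| | 1% vs 2% | 84% |

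Check by normal approximation for 15% vs 20%:

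- Pooled rate = (646×0.20 + 322×0.15)/968 = 0.1834.
- Null SE = sqrt(0.1834×0.8166×(1/646+1/322)) = 0.0264.
- Alternative SE = sqrt(0.20×0.80/646 + 0.15×0.85/322) = 0.0254.
- z = (0.05 − 1.96×0.0264)/0.0254 = −0.07, so power is about 47% and the miss rate about 53%, against 52% exactly.

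Enrolling the full 1065 (710/355 at the same ratio) changes little: approximate power for 20% vs 25% goes from 41% to 44%.

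**Step 2: rare events.** Seven laparoscopic deaths against none (7/646 = 1.1%) is not significant by either test: chi-square P=0.061, Fisher P=0.103. Fisher's test needs 9 vs 0.

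**Step 3: chi-square alone for margins.** For 0/646 vs 2/322 positive DRMs, chi-square = 968×(0×320 − 2×646)²/(646×322×2×966) = 4.02. This gives P=0.045 in favour of laparoscopy; Fisher gives 0.11. With equal true rates the nominal error is 2.5% in each direction:

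| True rate, both arms | Test | Declares laparoscopy better | Declares it worse |
|---|---|---|---|
| 0.3% | chi-square | 4.2% | 0.03% |
| 0.3% | Fisher | 1.6% | 0.01% |
| 1% | chi-square | 2.9% | 1.7% |
| 3% | chi-square | 2.8% | 2.3% |

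**Step 4: what an interval would show.** Half-width at equal rates = 1.96×sqrt(p(1−p)(1/646+1/322)). At p=15% this is 1.96×0.0244 = 4.8 points, and at p=3% it is 1.96×0.0116 = 2.3 points.

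**The case against.** These are secondary outcomes, and tests of difference with counts and percentages are common for them. The shells are headed as a proposed format. Other cells that will plainly be filled are also blank, such as the by-stage rows for margin length and lymph nodes, and the mortality placeholder may be a template slip. In the copy reviewed, Table 5's margin rows run into a fragment without column heads. The counts will be published, so a reader could compute the intervals. All of this limits the weight of the gap. It does not remove it, because the SAP text asks for no interval on these outcomes either.

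Four stronger readings are tempting and not supported:

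- *A relevant harm would usually be missed.* This holds for the mortality scenarios and for by-stage CRM at 3% vs 6%. For overall complications and CRM the moderate scenarios are split, with three of six missed less than half the time, and larger excesses are mostly detected.
- *No intervals are planned for safety or pathology.* They are planned for TME quality, every listed complication and every Clavien-Dindo grade.
- *The plan already equates non-significance with safety.* The SAP Background sentence "Many meta-analyses have found no significant differences between the two surgical approaches" concerns recurrence, metastasis and DFS in past studies, not 30-day safety, and the Background adds that such findings need further discussion. No passage says that P>=0.05 will be read as safe; the plan simply does not guard against it.
- *The chi-square test is biased for margins generally.* The imbalance matters only at rates below about 1%. Fisher's test does not fully remove it, and it costs some power: for 0.3% vs 1.3%, 21% against 28%.

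**Conclusion.** The point stands in limited form. Total 30-day complications, 30-day mortality and negative CRM and DRM are assessed only by two-sided tests of no difference, and neither the SAP text nor the shells plan a risk-difference interval for them. At 646 vs 322, a 5-point excess in complications from a 10-20% base would be missed 41-59% of the time, and a 3-point excess in positive CRM from a 2-5% base 34-60%. A rise in mortality from 0.5% to 1.5%, or from 1% to 2%, would be missed more than 80% of the time. A 10-point excess in complications from a 15-20% base would be missed only 4-8% of the time. These sizes rest on assumed event rates and on the planned arm sizes. The absence of intervals for these rows does not depend on those assumptions.

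**What to change.** 1. In SAP 8.3.3 (1) and (9) and Tables 5 and 6, report the risk difference (laparoscopic minus open) with a 95% score-type CI, for example Miettinen-Nurminen. Do this for total 30-day complications, 30-day mortality, and CRM and DRM positivity, and for margins also by stage.
2. Add to SAP 8.4 that P>=0.05 is not evidence of safety or comparability, and that the upper confidence limit is to be reported as the excess risk not ruled out. This sets no new margin.
3. In item (1), allow Fisher's exact test for margin positivity when an expected count is below 5, as items (8) and (9) already permit the exact test. At the planned sizes the overall comparison would switch at 15 or fewer positive specimens (15×322/968 = 4.99). This reduces false claims in favour of laparoscopy when positives are very rare, without fully removing the imbalance, and slightly lowers power.

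The cost is SAP wording and a few table cells, with no new data or patients. The safety statement becomes less favourable, because the intervals will show about ±4.8 points at 15% complications and ±2.3 points at 3% positive margins.

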### **Analysis of secondary outcome measures**

- Pathologic outcomes, including the TME quality, negative CRM, and negative DRM, are presented as numbers (percentage) and compared using the Chi-square test.
- The operation time (min) and estimated blood loss (ml) are compared between the groups by the Wilcoxon method.
- The OS is calculated using the Kaplan-Meier method after the last participant has been enrolled for three years. The median OS time and its 95% confidence interval are compared between the two groups using the log-rank test.
- The OS when the last participant is enrolled for five years is determined by using the Kaplan-Meier method. The median OS time and its 95% confidence interval are compared between the two groups using the log-rank test.
- Time to tumor recurrence is determined using the Kaplan-Meier method. The median time of recurrence and its 95% confidence interval are compared between the two groups using the log-rank test.
- The perioperative recovery time is compared between the groups using the Wilcoxon method.
- The length of postoperative hospital stay (d) is compared between the groups using the Wilcoxon method.
- The incidence of intraoperative complications is compared between the groups by the  $\chi^2$  test or Fisher's exact probability method.
- After surgery, the incidence of complications and 30-day mortality rate are compared using the  $\chi^2$  test or the Fisher's exact tests for probability.

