## 8 Statistical analyses

### 8.1 Sample size estimation

The sample size was estimated using a log-rank test based on a 3-year DFS with a noninferiority margin of 10%. At the time of this trial design, a noninferiority margin of 10% was determined to be clinically acceptable. Considering distinct prognoses in patients with stage I versus II/III disease, the sample size was calculated separately. Assumptions for the 3-year DFS rate in the open surgery group were 94.3% and 75.2% for clinical stage I and II/III diseases, respectively, with 359 patients with stage I disease (laparoscopic 240, open 119), 609 patients with stage II/III disease (laparoscopic 406, open 203), and a total of 968 patients (laparoscopic 646, open 322) were required to provide an 80% power with a one-sided  $\alpha$  of 2.5%. One thousand sixty-five patients were aimed to enroll to allow for exclusions after

randomization to maintain the required statistical power. All calculations allowed for a 20% dropout. The planned and follow-up period were three years and five years, respectively.

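### Margin status is assigned the chi-square test alone, with no exact-test fallback; if positive margins are rare, two positives in the open arm against none could be called significant.

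*Combined protocol and SAP*

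**What the plan says.** SAP 8.3.3, secondary item (1), sets the test for the pathologic outcomes: "Pathologic outcomes, including the TME quality, negative CRM, and negative DRM, are presented as numbers (percentage) and compared using the Chi-square test". Protocol 12.2, under the secondary outcome analysis, carries the same instruction: "negative CRM, and negative DRM, are presented as numbers (percentage) and compared using the Chi-square test". Neither place offers an alternative for small counts, and neither says whether the chi-square is continuity-corrected.

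The same SAP list treats other binary outcomes differently. Item (8), intraoperative complications, allows the chi-square "test or Fisher's exact probability method". Item (9), postoperative complications and 30-day mortality, allows the chi-square "test or the Fisher's exact tests for probability".

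SAP 8.4 gives the general rule: "Generally, two-sided tests are used for statistical analysis", and a P value below 0.05 "indicates that the difference is statistically significant". The planned arm sizes are in SAP 8.1: "a total of 968 patients (laparoscopic 646, open 322) were required". Protocol 10.2 defines a positive margin as cancer cells within 1 mm of the cut edge. No document gives an expected rate of positive margins.

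**The concern.** The large-sample chi-square approximation is poor when expected counts are small, and here the smaller arm is about half the size of the larger. If positive margins turn out to be rare, a literal reading of item (1) would apply that approximation where items (8) and (9) would permit an exact test.

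A handful of events could then carry a significant P value on an oncologic secondary outcome. Because the type of chi-square is not stated, the call on the same data could also depend on a choice made after the data are seen.

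**Working it through.** The plan states no rate, power or P value for the margin comparison, so there is no figure of its own to reproduce.

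**Inputs.** Arms of 646 and 322 (SAP 8.1); two-sided P<0.05 (SAP 8.4). The 2:1 allocation is inferred from the arm sizes: 646/322 = 2.01, and for stage II/III ("609 patients with stage II/III disease (laparoscopic 406, open 203") 406/203 = 2.00. The true positive-margin rate is an assumption, varied below.

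**When expected counts fall below 5.** The smallest expected count is 322 × (total positives)/968. With 15 positives it is 322 × 15/968 = 4.99; with 16 it is 5.32. The problem therefore arises at about 15 or fewer positives in total, and 15/968 is about 1.5%.

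**One illustrative result: 0/646 laparoscopic, 2/322 open.** The smallest expected count is 322 × 2/968 = 0.67.

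- Pearson, uncorrected: N(ad−bc)² / product of the margins = 968 × (0×320 − 646×2)² / (646 × 322 × 2 × 966) = 4.02, P = 0.045.
- Pearson, continuity-corrected: 968 × (1292 − 484)² / (646 × 322 × 2 × 966) = 1.57, P = 0.21.
- Fisher: the probability that both positives fall in the open arm is (322 × 321)/(968 × 967) = 0.110. Every other split of two positives is more probable, so the two-sided P = 0.110.

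Fisher reaches significance only at 0 v 3 (P = 0.037). In the other direction, 2 laparoscopic v 0 open gives Pearson P = 0.32, 7 v 0 gives 0.061, and 8 v 0 is needed for 0.045 (Fisher 0.058).

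**Error rates with equal true rates in both arms.** These come from full enumeration of two binomials with n = 646 and 322, counting a rejection when P<0.05.

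| True positive rate | Pearson: open worse | Pearson: laparoscopic worse | Fisher: open worse | Fisher: laparoscopic worse | Pearson total | Fisher total |
|---|---|---|---|---|---|---|
| 0.3% | 4.18% | 0.03% | 1.62% | 0.01% | 4.2% | 1.6% |
| 0.5% | 3.55% | 0.35% | 2.42% | 0.12% | 3.9% | 2.5% |
| 1% | 2.94% | 1.69% | 2.40% | 1.01% | 4.6% | 3.4% |
| 2% | 2.93% | 2.13% | 2.07% | 1.74% | 5.1% | 3.8% |

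An even split of the two-sided 5% would put 2.5% in each direction. Pearson exceeds this clearly for open worse at 0.3% and 0.5%, and only slightly from 1% upwards.

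**The case against.** Several points on the other side are sound.

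- **Total error is controlled.** Pearson's two-sided size lies between 2.2% and 5.1% for true rates from 0.1% to 2%. The 2.5%-per-direction benchmark is a reviewer's yardstick here; in the SAP, 2.5% is the one-sided level of the primary test.
- **Fisher does not remove the lopsidedness.** A reader might infer that the chi-square test is what tilts false positives towards laparoscopy. The tilt comes from sparse data in 2:1 arms. At a 0.5% rate the two directions stand at 3.55% v 0.35% under Pearson (about 10:1) and 2.42% v 0.12% under Fisher (about 20:1). Fisher lowers the open-worse error but does not balance the two.
- **Rarity and the uncorrected test are assumptions.** Nothing in the documents shows that positive CRM or DRM will be below about 1.5%, and with a continuity correction the example is not significant.
- **Stage-level tests are not clearly planned.** SAP Table 5 tabulates margins by stage but shows one P cell per margin, on the heading row, whereas TME quality has a P cell for each stage. Error rates for a stage I margin test would concern a comparison that the SAP does not clearly specify.
- **A mid-P test is not what the plan already allows.** Items (8) and (9) name Fisher and give neither a mid-P variant nor an expected-count trigger. Mid-P is also not uniformly better: in stage I (240 v 119) at a 3% rate, using it for small expected counts raises the open-worse error from 2.7% to 3.2%.
- **The protocol defers detail.** Protocol section 12 leaves its methods to be finalised in the SAP before database lock. That softens the protocol sentence, but the SAP sentence remains.

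What stands is the gap itself: one item lacks a fallback that its neighbours have, and on sparse data the named test can give a significant result that an exact test would not.

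**Conclusion.** The point holds as a minor improvement. SAP 8.3.3(1) and protocol 12.2 should not confine margin status to the chi-square test when other binary outcomes may use Fisher. The size is a false open-worse rate of 4.2% at a 0.3% true rate and 3.6% at 0.5%, against 1.6% and 2.4% with Fisher. By a 2% rate Pearson's open-worse error is 2.9%, close to the benchmark, and the expected number of positives (968 × 0.02, about 19) is above the range in which the approximation is in doubt.

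This rests on three assumptions: positive margins are rare, the chi-square is uncorrected, and the arms are near 646 and 322. It does not support saying that overall type I error is inflated, that the plan is biased in favour of laparoscopy in a way Fisher would cure, or that the noninferiority conclusion is at risk. The primary disease-free survival analysis is unaffected.

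**What to change.** In SAP 8.3.3(1) and the matching sentence of protocol 12.2, extend the chi-square-or-Fisher option of items (8) and (9) to margin status. State the rule: Fisher's exact test when any expected count is below 5, chi-square otherwise. Apply the same rule at any stage level where a margin P value is reported.

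This is one line of text and needs no new data. The cost is that Fisher is slightly conservative: at a 1% true rate with 646 and 322 patients, rejections in the laparoscopic-worse direction under equal true rates fall from 1.7% to 1.0%.
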